
### Randomisation

After completion of all the screening evaluations (all the inclusion criteria satisfied and none of the exclusion criteria apply) and signature of the informed consent(s), all eligible patients will be randomly assigned by the randomisation center of the French Federation of Digestive Oncology (FFCD) to one of the treatment arms according to the RAS status: *RAS* WT patients will be randomised between 3 treatment arms (Arm A vs. Arm B vs. Arm C) and those mutated for RAS between 2 treatement arms (Arm A vs. Arm C). The randomization will be stratified according to the investigator center, T stage (T1/2/3 vs. T4) of the primary tumor on the pretreatment CT scan and N stage (N0-N1 vs. N2) of the primary tumor on the pretreatment CT scan. The screening/baseline assessment will take place within the 3 weeks prior to randomization, randomization will be done between 4 and 8 weeks after surgery and the maximum time between randomization and treatment start will be 15 days.

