## Methods/Design

### Protocol overview

The Prodige 22 - ECKINOXE trial is a multicenter randomized phase II trial designed to evaluate efficacy (response rate) and feasibility (safety, tolerability) of two chemotherapy regimens (FOLFOX-4 alone and FOLFOX-4 + Cetuximab) in a peri-operative setting in patients with stage II/III CC. Control arm includes patients for whom standard treatment comprises surgery followed by adjuvant FOLFOX-4 chemotherapy. This phase II study will assess the feasibility of a peri-operative strategy in these patients and the impact of adding cetuximab in this setting for patients with *RAS* wild type tumors.

A double central, independent and blinded review of imaging and pathology is planned. All eligible patients will be randomized to either surgery alone or neoadjuvant chemotherapy with simplified FOLFOX-4. Patients randomized to the simplified FOLFOX-4 arm will be randomized to receive Cetuximab or not if they are *RAS* WT

Thus based on the *RAS* status of the primary tumor the design will be: Arm A vs. Arm B vs. Arm C for *RAS* WT patients and Arm A vs. Arm C for those *RAS* mutated (Fig. 1)

Arm A: simplified FOLFOX-4 alone every 2 weeks for 4 cycles, followed by colectomy, followed by simplified FOLFOX-4 alone every 2 weeks for 8 cycles.

Arm B: Cetuximab plus simplified FOLFOX-4 every 2 weeks for 4 cycles, followed by colectomy, followed by Cetuximab plus simplified FOLFOX-4 every 2 weeks for 8 cycles.

Arm C (control arm): Colectomy followed by simplified FOLFOX-4 alone every 2 weeks for 12 cycles. Adjuvant chemotherapy will be given to all patients with stage III CC and according to the local practices for stage II cancer.

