### Exclusion criteria

Patients are not eligible for this study if any of the following exclusion criteria apply: (i) contra-indication to iodinated contrast medium injection including allergy to iodinated contrast medium and renal insufficiency proscribing iodinated injection; (ii) rectal cancer located within 15 cm from the anal verge by endoscopy or under the peritoneal reflection at surgery or having received radiation therapy prior to surgery; (iii) complicated primary CC (obstruction, bleeding, perforation); (iv) synchronous colorectal cancer; (v) metastatic spread at baseline assessment (lung, liver, peritoneal); (vi) history or current evidence on physical examination of central nervous system disease or; (vii) peripheral neuropathy ≥ grade 1 Common Toxicity Criteria for Adverse Events (CTCAE) v.3.0; (viii) known hypersensitivity reaction to any of the components of study treatments; (ix) presence of inflammatory bowel disease; (x) HNPCC syndrome or polyposis; (xi) major surgical procedure, open biopsy or significant traumatic injury within 28 days prior to study treatment start. Incompletely healed wounds or anticipation of the need for major surgical procedure during the course of the study; (xii) clinically relevant coronary artery disease or history of myocardial infarction in the last 12 months, or high risk of uncontrolled arrhythmia; (xiiii) pregnancy (absence to be confirmed by ß-hCG test) or breast-feeding period; (xiv) previous malignancy in the last 5 years; (xv) medical, geographical, sociological, psychological or legal conditions that would not permit the patient to complete the study or sign informed consent; (xvi) any significant disease which, in the investigator’s opinion, would exclude the patient from the study.

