### Treatment methods

The treatment protocols are standardized with regard to radiological and pathological parameters, based on the recommendations of I’INCa, the FFCD, the French Society of Pathology, the French Society of Digestive Endoscopy and the French Society of Digestive Surgery. Treatment application depends on the *RAS* status of the primary tumor (Fig. 1) and must start within 14 days after the randomisation.

Neoadjuvant chemotherapy requires an implantable subcutaneous venous access and will be administrated for 4 cycles. The following assessments will be performed prior to each cycle (every two weeks) before chemotherapy administration: documentation of concomitant medication and concurrent procedures; physical examination; vital signs and ECOG performance status; blood sampling for hematology and clinical biochemistry and recording of adverse events since last cycle (including primary tumor related symptoms or complications). The end of treatment visit must be performed 15 days after the 4^th^ cycle administration.

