#### FOLFOX-4 + Cetuximab chemotherapy

Patients in Arm B only will receive Cetuximab according the same schedule of the FOLFOX chemotherapy, i.e. once every two weeks (on d1, d14, d28, etc.…). Cetuximab will always be administered first, i.e. the Cetuximab infusion should be completed one hour before chemotherapy begins. The Cetuximab dose must always be based on the body surface area (BSA). There is no restriction for Cetuximab in patient with a BSA > 2.0 m^2^. The dosage and administration procedure for Cetuximab is as follows:

- The first infusion is 500 mg/m^2^. As prophylaxis to reduce the risk of an allergic/hypersensitivity reaction, it is mandatory to pretreat the patient as specified below. Cetuximab is administered as follows: the volume is administered over 120 minutes (maximum rate of 5 mL/min). Saline solution (0.9 %) is used to flush the line at the end of the infusion. Vital signs are checked before, during, immediately after and 1 hour after the end of the infusion.

The subsequent weekly doses are 500 mg/m^2^. Cetuximab is administered as follows: the volume is administered over 60 minutes (maximum rate of 10 mL/min). Saline solution (0.9 %) is used to flush the line at the end of the infusion.

Surgery will be performed 3 to 5 weeks after the last cycle of neoadjuvant chemotherapy (in arms A and B) or within 14 days after the randomisation. The anesthetic evaluation, patient’s information regarding the operative procedure and the organization of the hospitalization will be performed according to the local practices of each investigator center. The colectomy will be performed by laparotomy or laparoscopy (investigator discretion) with respect of the oncological quality criteria of resection. Per and postoperative data will be collected and reported in specific forms.

Adjuvant chemotherapy will be administrated for all patients included in arms A (FOLFOX-4) and B (FOLFOX-4 + Cetuximab). Eight additional cycles will be administrated (for a total of 12 cycles) according the same regimen. In Arm C (control Arm), only patients with stage III CC (on pathological examination) will receive 12 cycles of adjuvant chemotherapy. For those with stage II CC, the decision of adjuvant chemotherapy in this arm will be will be done according to the investigator's discretion.

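### The Randomisation section places randomisation 4 to 8 weeks after surgery, whereas the design places colectomy after randomisation in every arm

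*Protocol article*

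**What the plan says.** The protocol article gives the order of randomisation and surgery in several places.

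- **Randomisation:** "randomization will be done between 4 and 8 weeks after surgery and the maximum time between randomization and treatment start will be 15 days".
- **Protocol overview, arm A:** "simplified FOLFOX-4 alone every 2 weeks for 4 cycles, followed by colectomy", then further chemotherapy. Arm B has the same sequence with cetuximab added.
- **Protocol overview, arm C:** "Colectomy followed by simplified FOLFOX-4 alone every 2 weeks for 12 cycles".
- **Surgery paragraph (under FOLFOX-4 + Cetuximab chemotherapy):** colectomy is set 3 to 5 weeks from the final pre-operative cycle "in arms A and B) or within 14 days after the randomisation". The second option can only be arm C.
- **Treatment methods:** treatment "must start within 14 days after the randomisation".
- **Exclusion criteria (xi), second sentence:** "Incompletely healed wounds or anticipation of the need for major surgical procedure during the course of the study".
- **Endpoints:** recurrence-free survival, disease-free survival and time to quality-of-life deterioration are all measured from randomisation.

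**The concern.** A window that opens 4 weeks after surgery would suit a trial that allocates purely postoperative treatment. Here the randomised question is whether chemotherapy is given before colectomy, so the colon tumour must still be in place when the patient is allocated.

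The clause is the only sentence in the article that states when randomisation happens relative to surgery as a rule in its own right, and it reverses the design. Three things depend on it:

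- **Delivery of arms A and B.** A patient who has already had a colectomy cannot receive neoadjuvant treatment.
- **The primary endpoint.** TRG on the resected tumour measures response to pre-operative chemotherapy only if allocation and treatment come before resection.
- **Time zero.** The randomisation date starts the clock for both survival endpoints and for time to quality-of-life deterioration. It also anchors the screening and treatment-start windows.

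Two smaller wording problems touch the same part of the plan: different limits on the time to treatment start, and an exclusion on anticipated major surgery that does not mention the planned operation.

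**Working it through.** The article gives no figure for the interval from randomisation to surgery, so there is none to reproduce. The check is a day count with randomisation as day 0.

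**Inputs, all from the protocol article**

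- Randomisation to treatment start: 0 to 14 days (Treatment methods) or 0 to 15 days (Randomisation).
- Four pre-operative cycles, one every 14 days (Protocol overview), so day 1 of cycle 4 is 3 × 14 = 42 days after day 1 of cycle 1.
- Last cycle to surgery in arms A and B: 3 to 5 weeks, or 21 to 35 days (surgery paragraph).
- Randomisation to surgery in arm C: 0 to 14 days (surgery paragraph).
- Window under test: surgery 4 to 8 weeks before randomisation, or day −56 to day −28 (Randomisation).

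**Arms A and B, counting from day 1 of cycle 4**

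Surgery day = start lag + 42 + interval to surgery.

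- Earliest: 0 + 42 + 21 = 63 days (9.0 weeks).
- Latest: 14 + 42 + 35 = 91 days (13.0 weeks), or 15 + 42 + 35 = 92 days (13.1 weeks) with the 15-day limit.

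**Arms A and B, counting from the end of the 14-day fourth cycle**

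- Earliest: 63 + 14 = 77 days (11.0 weeks).
- Latest: 91 + 14 = 105 days (15.0 weeks), or 92 + 14 = 106 days (15.1 weeks).

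**Comparison**

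| | Surgery day by the treatment schedule | Surgery day needed by the Randomisation clause |
|---|---|---|
| Arms A and B, from start of cycle 4 | +63 to +92 | −56 to −28 |
| Arms A and B, from end of cycle 4 | +77 to +106 | −56 to −28 |
| Arm C | 0 to +14 | −56 to −28 |

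The windows overlap in no arm. The narrowest gap is 0 − (−28) = 28 days in arm C and 63 − (−28) = 91 days in arms A and B.

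**Consistency within the Randomisation section**

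That section stratifies on T and N stage of the primary tumour on the pretreatment CT scan, and sets screening within 3 weeks before randomisation. If randomisation came 28 to 56 days after surgery, screening would fall between 28 − 21 = 7 days and 56 days after surgery. The baseline CT, which is part of that work-up, would then be staging a tumour already removed.

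**Could the word surgery mean another operation?**

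The only earlier operation the article foresees is a defunctioning stoma, mentioned in the Inclusion criteria for patients with obstruction. That is a subset, whereas the clause covers every patient.

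**Treatment-start limits**

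A patient starting on day 15 complies with the Randomisation section and breaches Treatment methods.

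**The case against.** The best defence is that no one could act on the clause. The Protocol overview puts colectomy after allocation in each arm, the surgery paragraph times it from randomisation or from the last neoadjuvant cycle, RAS status comes from diagnostic biopsies, stratification uses the pretreatment CT, and the Endpoints section contrasts tumours operated on at once with tumours treated first. Randomisation is done centrally. Sites would very probably see the clause as stray and follow the design, so the article offers no likely route to corrupted TRG or survival data.

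Much of this stands: it bears on how likely the harm is. It does not make the clause correct. This is a complete sentence that states a rule, not a detail left to a fuller document, and compliance with it cannot be audited because the design cannot meet it.

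A reader might infer two stronger points that the documents do not support.

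- **Time zero would shift in arm C only.** Allocation is unknown until randomisation, so a pre-randomisation rule cannot be applied to one arm. If the clause were followed, every patient would already have had a colectomy. The displacement would affect all patients and is not a differential bias between arms.
- **Exclusion (xi) makes every patient ineligible.** This needs a hyper-literal reading. The first sentence of (xi) concerns major surgery shortly before study treatment starts, and colectomy is itself a component of every arm. The natural meaning is surgery other than the planned operation. Stating the exception would help, but the criterion does not empty the trial.

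**Conclusion.** The contradiction is real, and no reading removes it for all patients. The Randomisation section requires surgery 28 to 56 days before randomisation. The treatment schedule puts it 63 to 92 days after randomisation in arms A and B (77 to 106 days if the interval runs from the end of cycle 4) and 0 to 14 days after it in arm C. The range for arms A and B assumes that all four cycles run on schedule and depends on how the last cycle is counted; the conclusion holds on either count.

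The consequences described above are conditional on the clause being followed as written. The day counts measure the conflict in the text, not an effect on any analysis. The 14-day versus 15-day mismatch is genuine but minor, and exclusion (xi) needs only clarification.

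**What to change.** In the Randomisation section, delete the clause that dates randomisation from surgery. State instead that, in all arms, randomisation precedes all study treatment, including colectomy, in line with the Protocol overview and the surgery paragraph. The existing 3-week screening window before randomisation can stay.

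Make two minor edits at the same time:

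- Reconcile the 14-day limit in Treatment methods with the 15-day limit in the Randomisation section, so that one figure applies throughout. The choice is for the sponsor.
- Clarify that the anticipated major surgery in exclusion (xi) means surgery other than the protocol colectomy.

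The cost is a wording amendment. It adds no patients or procedures and changes no calculation.

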### Pre-therapeutic work-up

The screening visit must be performed within 3 weeks before the randomisation. During this visit, inclusion and exclusion criteria are checked and validated. The complete pre-therapeutic work-up includes a physical examination, standard laboratory tests with CEA level, complete colonoscopy with biopsies and a CT scan of the thorax, abdomen and pelvis. Clinical tumoural staging (cTNM) will be based on the data obtained from CT scan. The determination of the *RAS* status (*KRAS* and *NRAS* mutations located within the exons 2, 3 and 4) of the primary tumor will be performed from biopsies obtained during the diagnostic colonoscopy, by each centers at the “plateformes de génétique somatique des tumours” labelled by the National Institut of Cancer (INCa). Once baseline assessments are completed, check and validation of inclusion and exclusion criteria for the study will be performed at the oncological multidisciplinary meeting of each center.

### Treatment methods

The treatment protocols are standardized with regard to radiological and pathological parameters, based on the recommendations of I’INCa, the FFCD, the French Society of Pathology, the French Society of Digestive Endoscopy and the French Society of Digestive Surgery. Treatment application depends on the *RAS* status of the primary tumor (Fig. 1) and must start within 14 days after the randomisation.

Neoadjuvant chemotherapy requires an implantable subcutaneous venous access and will be administrated for 4 cycles. The following assessments will be performed prior to each cycle (every two weeks) before chemotherapy administration: documentation of concomitant medication and concurrent procedures; physical examination; vital signs and ECOG performance status; blood sampling for hematology and clinical biochemistry and recording of adverse events since last cycle (including primary tumor related symptoms or complications). The end of treatment visit must be performed 15 days after the 4^th^ cycle administration.

#### FOLFOX-4 chemotherapy

The simplified FOLFOX-4 (Oxaliplatine, ELOXATINE^R^ (85 mg/m^2^), with simplified LV5FU2) is administrated intravenously over 48 hours once every two weeks (i.e. on d1/d2, d15/d16, d29/d30 etc.). The FOLFOX-4 regimen will be administrated as follows: Oxaliplatin will be administered as an 85 mg/m^2^ intravenous infusion over 2 hours (on day 1 only) concomitantly with LV, as a 400 mg/m^2^ infusion over 2 hours, followed by 5- fluorouracil (5-FU), given as a 400 mg/m^2^ bolus injection (over 10 minutes), and then as a 2400 mg/m^2^ continuous infusion over 46 hours. Cycle length is 2 weeks comprising 48 hours of infusion and 12 days of rest. These cycles must be repeated every second week. A total of 12 cycles (4 cycles preoperatively, 8 cycles postoperatively) will be administrated to all patients in Arm A and B. In Arm C (control Arm), only patients with stage III CC (on pathological examination) will receive 12 cycles of adjuvant chemotherapy. For those with stage II CC, the decision of adjuvant chemotherapy in this Arm will be will be done according to the investigator discretion.

#### FOLFOX-4 + Cetuximab chemotherapy

Patients in Arm B only will receive Cetuximab according the same schedule of the FOLFOX chemotherapy, i.e. once every two weeks (on d1, d14, d28, etc.…). Cetuximab will always be administered first, i.e. the Cetuximab infusion should be completed one hour before chemotherapy begins. The Cetuximab dose must always be based on the body surface area (BSA). There is no restriction for Cetuximab in patient with a BSA > 2.0 m^2^. The dosage and administration procedure for Cetuximab is as follows:

- The first infusion is 500 mg/m^2^. As prophylaxis to reduce the risk of an allergic/hypersensitivity reaction, it is mandatory to pretreat the patient as specified below. Cetuximab is administered as follows: the volume is administered over 120 minutes (maximum rate of 5 mL/min). Saline solution (0.9 %) is used to flush the line at the end of the infusion. Vital signs are checked before, during, immediately after and 1 hour after the end of the infusion.

The subsequent weekly doses are 500 mg/m^2^. Cetuximab is administered as follows: the volume is administered over 60 minutes (maximum rate of 10 mL/min). Saline solution (0.9 %) is used to flush the line at the end of the infusion.

Surgery will be performed 3 to 5 weeks after the last cycle of neoadjuvant chemotherapy (in arms A and B) or within 14 days after the randomisation. The anesthetic evaluation, patient’s information regarding the operative procedure and the organization of the hospitalization will be performed according to the local practices of each investigator center. The colectomy will be performed by laparotomy or laparoscopy (investigator discretion) with respect of the oncological quality criteria of resection. Per and postoperative data will be collected and reported in specific forms.

Adjuvant chemotherapy will be administrated for all patients included in arms A (FOLFOX-4) and B (FOLFOX-4 + Cetuximab). Eight additional cycles will be administrated (for a total of 12 cycles) according the same regimen. In Arm C (control Arm), only patients with stage III CC (on pathological examination) will receive 12 cycles of adjuvant chemotherapy. For those with stage II CC, the decision of adjuvant chemotherapy in this arm will be will be done according to the investigator's discretion.

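### The cetuximab section states the frequency of infusions after the first in two incompatible ways, two-weekly and weekly, and its day labels sit one day off the FOLFOX days

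*Protocol article*

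**What the plan says.** Four statements in the protocol article bear on when cetuximab is given.

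- **Protocol overview:** "Arm B: Cetuximab plus simplified FOLFOX-4 every 2 weeks for 4 cycles", then colectomy, then eight further cycles, again at two-week intervals.
- **FOLFOX-4 + Cetuximab chemotherapy, opening:** "Patients in Arm B only will receive Cetuximab according the same schedule of the FOLFOX chemotherapy", spelled out as "once every two weeks (on d1, d14, d28, etc". The section adds that cetuximab always comes first and that its infusion is to finish an hour ahead of chemotherapy.
- **Same section, dosing text:** "The first infusion is 500 mg/m^2" and, for everything after it, "The subsequent weekly doses are 500" mg/m².
- **FOLFOX-4 chemotherapy:** the chemotherapy days are given as "on d1/d2, d15/d16, d29/d30 etc", with a two-week cycle and 12 cycles in all for Arms A and B (4 before and 8 after surgery).

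**The concern.** The dosing sentence is the only one that sets the dose of the second and later cetuximab infusions, so it is where a reader looks for them. It calls those doses weekly, while the opening of the same section makes them two-weekly. The amount per infusion is 500 mg/m² on either reading, so the dose figure gives no hint that something is wrong; the frequency word alone determines exposure.

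Two things are at stake.

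- **Safety.** Under Treatment methods, the examination, blood tests and adverse-event review during neoadjuvant chemotherapy come before each two-week cycle. The article lists no check before an infusion given between cycles.
- **Interpretation.** Under Statistical analysis and sample size, Arm B is judged on small counts: at most 1 or at least 2 TRG1 responses in the first 13 patients, at most 6 or at least 7 in 33, and a 10 % limit on serious complications within 60 days of surgery. Ten per cent of 33 is 3.3, so four patients reach the limit. If exposure differed between centres, these counts would describe a mixture of two regimens.

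The day labels are a second and lesser conflict. The section says the two drugs share a schedule, yet the listed days do not coincide after day 1.

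**Working it through.** The article gives no cumulative cetuximab dose or dose intensity, so there is no stated figure to reproduce. The check is arithmetic on the stated dose and the two stated frequencies.

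**Inputs**

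- 500 mg/m² for the first and for each later infusion (cetuximab section)
- two-week cycles, 4 pre-operative and 8 post-operative (FOLFOX-4 section)
- interval between infusions of 2 weeks (Protocol overview; cetuximab section, opening) or 1 week (cetuximab section, dosing text)

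**Dose intensity after the first infusion** = dose / interval

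- Two-weekly: 500 / 2 = 250 mg/m² per week
- Weekly: 500 / 1 = 500 mg/m² per week
- Ratio: 500 / 250 = 2.0

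**Cumulative dose** = 500 × number of infusions

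The article does not say when weekly dosing would end, so two assumptions are shown: (a) it runs to the end of the last two-week cycle of each phase; (b) it ends on day 1 of that cycle. For c cycles, the two-weekly reading gives c infusions, (a) gives 2c, and (b) gives 2(c − 1) + 1.

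| Phase | Two-weekly | Weekly, (a) | Weekly, (b) |
|---|---|---|---|
| Pre-operative, 4 cycles | 4 × 500 = 2000 | 8 × 500 = 4000 (ratio 2.0) | 7 × 500 = 3500 (ratio 1.75) |
| Post-operative, 8 cycles | 8 × 500 = 4000 | 16 × 500 = 8000 (ratio 2.0) | 15 × 500 = 7500 (ratio 1.875) |
| Both phases, 12 cycles | 6000 | 12000 (ratio 2.0) | 3500 + 7500 = 11000 (ratio 1.83) |

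All doses are in mg/m².

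**Days**

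- A 14-day interval from day 1 gives day 1 + 14k: days 1, 15, 29. These are the FOLFOX days in the article.
- The cetuximab list is days 1, 14, 28. Its first interval is 14 − 1 = 13 days and its second is 28 − 14 = 14 days.
- The difference from FOLFOX is 15 − 14 = 1 day and 29 − 28 = 1 day: a constant offset from cycle 2, not a growing drift.
- An infusion on day 14 cannot both follow the FOLFOX schedule and finish one hour before chemotherapy that starts on day 15.

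The sample size and the two-stage decision limits use response counts and rates only. They do not depend on the cetuximab schedule.

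**The case against.** The strongest reply is that the article's statements are lopsided. The Protocol overview puts Arm B on two-week intervals both before and after colectomy. The cetuximab section opens with the same interval, and its rule on finishing an hour before chemotherapy ties each infusion to a chemotherapy day, which an infusion in a week without chemotherapy could not meet. The pre-cycle checks are two-weekly as well. Against all this stands one adjective in one sentence.

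That stands as a limit on the point. A reader might infer that Arm B has no defined schedule, or that exposure is unknown by a factor of two. The text does not support that: a schedule is stated several times and contradicted once. It is inconsistent, not absent. The factor of two is exact for dose intensity only; for cumulative dose it depends on the assumed last infusion.

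A reader might also infer that Arm B's results cannot be interpreted. That would need centres to have dosed differently, and nothing in the article shows that they did. Sites treat from the full protocol, which is not at hand and may be consistent.

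The one-day offset is small, and it adds nothing to the difference in exposure.

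The reply does not remove the conflict. The odd sentence is current dosing text, not background, and counting how often each version appears is no safe way to settle an administration instruction.

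**Conclusion.** The point holds as a contradiction in the dosing instructions, and it must be fixed because it bears on patient safety and costs little to correct. Read literally, the two sentences differ by a factor of 2.0 in dose intensity after the first infusion. The cumulative dose differs by a factor of 1.75 to 2.0 before surgery and 1.83 to 2.0 over 12 cycles. The ranges rest on the two assumptions about when weekly dosing would stop, and on all planned cycles being given without delay or reduction.

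The one-day difference in labels is a separate inconsistency of minor weight.

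The consequence for Arm B's TRG1 and 60-day morbidity counts is conditional: they would mix two exposures only if centres acted on different sentences. Confidence is high for the conflict in the wording. Whether it reached the full protocol or the sites cannot be judged from the article.

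**What to change.** The sponsor should:

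1. reconcile the frequency wording in the Protocol overview and the cetuximab section to a single schedule;
2. reconcile the infusion days in the FOLFOX-4 and cetuximab sections, so that the day lists agree with the statements that the schedule is shared and that cetuximab finishes before chemotherapy (the Protocol overview lists no days and needs no change on this count);
3. check the full protocol for the same wording and, if it is there, correct it and notify sites.

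Which schedule is right is for the sponsor to state; this review takes no position on it. The cost is a wording correction and, if needed, a notice to sites. The sample size and decision limits do not change.
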